**FIG. 2. f2:**
[figure not shown]
Flow diagram of anticipated subject recruitment, enrollment, intervention allocation, and disposition status. We anticipate *N* = 48 people with SCI to complete the study. SCI, spinal cord injury; tAIH, therapeutic intermittent hypoxia; WALK_tSTIM_, transcutaneous spinal stimulation-enhanced walking therapy.

For Aim 1, our sample-size estimate focused on results from an earlier placebo-controlled clinical trial that reported that persons with incomplete SCI completed the 10-Meter Walk Test (10MWT) faster after tAIH + WALK (−4.3 ± 1.0 sec, faster relative to baseline) as compared to Placebo + WALK (0.9 ± 0.4 sec, slower relative to baseline).^6^ From these results, we conservatively estimated the standard deviation of the 10MWT time relative to baseline as 2.0 sec in Placebo + WALK_tSTIM_ and tAIH + WALK_tSHAM_ and 3.0 sec in tAIH + WALK_tSTIM_. The estimated difference between the change in tAIH + WALK_tSTIM_ and the change in Placebo + WALK_tSTIM_ was −5.2 sec, and that difference between tAIH + WALK_tSTIM_ versus tAIH + WALK_tSHAM_ was estimated as −3.14 sec. Assuming a 20% dropout rate with 16 completers per group, three outcome measures (10MWT, Timed Up and Go Test [TUG], and the 6-Minute Walk Test [6MWT]), and a significance level of 0.0167 adjusted for the three repeated outcomes,^20^ this study will have >99% statistical power in comparing tAIH + WALK_tSTIM_ versus Placebo + WALK_tSTIM_ and >81% statistical power in comparing tAIH + WALK_tSTIM_ versus tAIH + WALK_tSHAM_.

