### Randomization

Before enrolling the first study participant, a research statistician generated the balanced randomization scheme for treatment allocation at both clinical sites using the R Statistical Package.^21^ This method randomly assigns participants to one of three intervention groups (*N* = 20 per group): 1) tAIH + WALK_tSTIM_, 2) tAIH + WALK_tSHAM_, and 3) Placebo + WALK_tSTIM_ in blocks of 6 participants. Using this scheme, the site coordinator will assign each participant to their respective intervention group in the order in which they complete the walking practice sessions. Although the coordinator informs participants about their possible group assignment, they will be blinded to the treatment they receive (i.e., tAIH or Placebo, WALK_tSTIM_, or WALK_tSHAM_). The clinical raters and trainers will also be unaware of each participant's treatment assignment. Based upon reports from participants blinded during our previous tAIH study,^6^ >75% guessed incorrectly or were uncertain of the breathing intervention received, suggesting that our previous blinding and air delivery methods were effective.

We plan a similar integrity analysis for the stimulation sham protocols (no stimulation). Participants guess the interventions received at the end of each treatment session and indicate their guess confidence using a Likert scale.^22,23^ Using a contingency table and Fisher's exact test, we will determine whether the probability of correct guessing differs from chance.

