#### Therapeutic acute intermittent hypoxia (tAIH/Placebo)

Each participant receives eight ∼40-min tAIH sessions (2 weeks, four sessions per week) of tAIH or sham. A tAIH session consists of 15 episodes of 90-sec breathing low oxygen (F_I_O_2_ = 0.10 ± 0.02, i.e., 10% O_2_) or breathing room air (F_I_O_2_ = 0.21 ± 0.02, i.e., 21% O_2_) for sham with 60-sec intervals of room air (Fig. 4). We provide the treatments by a custom automated air delivery system as previously described.^32^ In brief, the delivery system alternately directs an air from a pressure-swing adsorption low-oxygen generator (HYP-123; Hypoxico Inc., New York, NY) and a flow-matched blower source to the non-rebreather face mask. We monitor and record SpO_2_ and HR at 1-sec intervals and BP every fifth breathing interval using a vital monitor (Masimo Root, Radical-7; Masimo Corp., Irvine, CA).

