#### Blood pressure

We will define a systemic hypertensive event as a systolic pressure exceeding 140 mm Hg and/or diastolic pressure exceeding 90 mm Hg.^46^ For each participant, we specifically record the hypertension incident rate, that is, the number of hypertensive events divided by units of person-measures (the total number of BP measurements), which accounts for the total number of chances for detecting a hypertensive event and for measurements not made because of dropout or a disqualifying adverse event.^47^

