### Statistical analysis

We plan to test three subhypotheses using parametric and non-parametric statistical inference methods. Statistical significance corresponds to a *p* value <0.05.

#### Hypothesis 1

Daily tAIH + WALK_tSTIM_ enhances overground walking ability in persons with chronic SCI compared to tAIH + WALK_tSHAM_ or Placebo + WALK_tSTIM_.

We predict a decrease in 10MWT and TUG time and an increase in 6MWT distance relative to baseline after tAIH + WALK_tSTIM_ (vs. Placebo + WALK_tSTIM_, tAIH + WALK_tSHAM_). We quantify walking ability using three outcome measures: change in TUG, 10MWT, and 6MWT relative to baseline assessments. Change in performance on these measures will occur after the last intervention session and again at 1-, 4-, and 12-week post-intervention follow-ups (Fig. 3). We will test three related subhypotheses using a linear mixed model with intervention (tAIH + WALK_tSTIM_, tAIH + WALK_tSHAM_, and Placebo + WALK_tSTIM_) and time (visit number) as the fixed main effects, with subject as random effect, whereas scores for TUG (time), 10MWT (time), and 6MWT (distance) will be considered as repeated measures.^56^

Differences from assessment after completion of the walking practice sessions will be compared between and within interventions at tests (T_1_, T_2_) and follow-ups (1, 4, and 8 weeks post-intervention). If analyses of variance (ANOVAs) reveal significant differences, the Tukey-Kramer *post hoc* test will identify pair-wise differences. If walking performance measures at the end of the walking practice sessions are significantly different between intervention groups, we will use an analysis of covariance. We also plan to fit a linear mixed model to test the magnitude and duration of tAIH priming effects based on linear contrasts after controlling for the study period, baseline primary outcomes, and demographics data.

#### Hypothesis 2

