Daily tAIH priming enhances the potency of WALK_tSTIM_ on improving walking speed in people with chronic SCI. We quantify potency as the number of tAIH + WALK_tSTIM_ sessions (eight total) needed to achieve the MCID in walking speed.^57^ We assess walking speed with the 10MWT at the end of each training session and predict that those who receive tAIH + WALK_tSTIM_ will achieve an MCID with fewer training sessions than either treatment alone (Placebo + WALK_tSTIM_ or tAIH + WALK_tSHAM_). To test this hypothesis, we will use linear mixed models with number of sessions to achieve the MCID as the outcome with treatment group and 10MWT speed at baseline as fixed effects and participant as the random effect. We anticipate that improvement in walking recovery also will correlate with improved 6MWT, TUG, SCI-FAI, WISCI II, and LEMS scores, suggesting the clinical relevance of this intervention across impairment levels and walking deficits.

#### Hypothesis 3

Daily tAIH+WALK_tSTIM_ does not induce maladaptive changes (spasticity, pain, systemic hypertension, and AD) in persons with chronic SCI. We predict no difference in SCATS, NPRS, CVLT, O-TMT, NBDS, and NBSS scores after daily tAIH + WALK_tSTIM_ compared to baseline. We will use a Friedman two-way repeated-measures ANOVA by ranks to compare these relative scores between and within groups. Changes in these scores relative to baseline are the repeated measures. Intervention (tAIH + WALK_tSTIM_, Placebo + WALK_tSTIM_, and tAIH + WALK_tSHAM_) and time are the fixed main effects, with subject as the random effect. We also predict that tAIH + WALK_tSTIM_ will not elicit a greater incidence of systemic hypertension or AD in persons with chronic SCI.

To test these subhypotheses, we will compare the incidence rates of these maladaptive changes between interventions using the relative risk.^58,59^ A relative risk of 1 will indicate no association between the maladaptive measures and interventions. Using the 95% confidence interval of the relative risk,^59^ we will determine whether there is a statistically significant association between interventions. We predict that the relative risk of hypertension and AD are not different between tAIH versus placebo interventions and WALK_tSTIM_ versus WALK_tSHAM_ interventions.

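### The safety aim's only stated test for hypertension and autonomic dysreflexia is whether a relative risk is statistically significant, with no margin, unclear contrasts and no stated handling of repeated blood-pressure readings

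*Protocol article*

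**What the plan says.** Under Statistical analysis, Hypothesis 3, the article states that the combination does not induce spasticity, pain, systemic hypertension or AD. For hypertension and AD, incidence rates are compared between interventions by relative risk. The article explains that "A relative risk of 1 will indicate no association between the maladaptive measures and interventions", and the 95% confidence interval is used to judge whether an association is statistically significant. The expected result is then given by treatment component: "We predict that the relative risk of hypertension and AD are not different between tAIH versus placebo interventions and WALK_tSTIM_ versus WALK_tSHAM_ interventions". The general threshold is stated as "Statistical significance corresponds to a *p* value <0.05". No margin or largest acceptable ratio appears.

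The two rates have different denominators. Under Blood pressure, the hypertension rate is recorded for each participant as "the number of hypertensive events divided by units of person-measures (the total number of BP measurements". Under Autonomic dysreflexia incidence rate, the AD denominator is study days completed.

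Under Randomization, the scheme "randomly assigns participants to one of three intervention groups (*N* = 20 per group"): tAIH + WALK_tSTIM, tAIH + WALK_tSHAM and Placebo + WALK_tSTIM. The Sample size section says that the calculation supports Aims 1 and 2.

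**The concern.** Three features of this analysis bear on whether the safety aim can be answered.

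- **Decision rule.** The hypothesis is an absence of harm, but the rule can only detect a difference. If too few events occur to detect one, the expected finding appears whether or not harm exists.
- **Contrasts.** Placebo breathing occurs only with active stimulation, and sham stimulation only with tAIH. Two arms qualify as tAIH and one as placebo. If the two tAIH arms were pooled, the ratio would mix the tAIH effect with a difference in stimulation. The same holds for the stimulation contrast.
- **Repeated readings.** Blood-pressure readings within a person are correlated. An interval that treated them as independent would be too narrow and would produce false signals for hypertension.

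Safety is a named aim (Aim 3), so what is at stake is a published statement that the combination is free of these harms.

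**Working it through.** **Inputs from the article.** Three arms of 20; "Assuming a 20% dropout rate with 16 completers per group"; 15 breathing episodes per session over eight sessions; "BP every fifth breathing interval using a vital monitor". Event rates, the intraclass correlation (ICC) and the interval method are not given, so those below are assumptions.

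**The plan's own figures.** Hypothesis 3 has no stated power, event rate or margin to reproduce. The Aim 1 figures do reproduce. The standard error is √((3.0² + 2.0²)/16) = √(13/16) = 0.90 s. A two-sided t-test at 0.0167 then gives 99.9% power for 5.2 s and 82% for 3.14 s, against the stated >99% and >81%. Allowing for dropout, 16/(1 − 0.20) = 20 per arm.

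**1. How often the rule would flag real harm.** Take the participant-level risk of any event, with log-RR standard error √(1/a − 1/n + 1/c − 1/n), where a and c are the numbers of participants with an event in each arm. The chance that the 95% interval excludes 1 is summed over the two binomial distributions. Ranges reflect how zero cells are handled.

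| Assumed true risks | Per arm | Interval excludes 1 |
|---|---|---|
| 30% vs 10% (RR 3) | 20 | 10–13% |
| 30% vs 10% (RR 3) | 16 | 5–6% |
| 20% vs 10% (RR 2) | 16 | under 1% |
| 40% vs 20% (RR 2) | 16 | 9–12% |
| 60% vs 30% (RR 2) | 16 | 27–30% |

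Detection improves when events are common: a tripling from 20% is found in about 49% of trials with 16 per arm.

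Interval width at an observed RR of 1, 20% risk and 16 per arm (3.2 events per arm): exp(±1.96 × √(2 × 0.8/3.2)) = exp(±1.39), or 0.25 to 4.0. On the person-time scale used for AD, four events per arm give exp(±1.96 × √(2/4)), again 0.25 to 4.0. Sixteen events per arm would still give 0.5 to 2.0.

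**2. What pooling would do, if used.** Let b be the risk with neither treatment, let stimulation double it, let r be the true tAIH ratio, and let risks multiply with equal arms.

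- Placebo + WALK_tSTIM: 2b
- tAIH + WALK_tSTIM: 2br
- tAIH + WALK_tSHAM: br
- Pooled tAIH: (2br + br)/2 = 1.5br
- Pooled ratio: 1.5br/2b = 0.75r

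A harmless tAIH (r = 1) would show 0.75, and a true ratio of 1.33 would show 1.00. The pairwise contrast, 2br/2b = r, is unbiased.

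**3. What treating readings as independent would do, for hypertension only.** Fifteen episodes with a reading every fifth interval give about 3 readings per session, so about 24 over eight sessions before any others are counted. The design effect is 1 + (24 − 1) × ICC. At an ICC of 0.1 it is 3.3, and at 0.4 it is 10.2. The interval is then too narrow by its square root, 1.8 to 3.2 times on the log scale. In a beta-binomial simulation with 16 per arm and 15% of readings hypertensive, the false-positive rate was about 27–28%, 41–42% and 54–55% at ICC 0.1, 0.2 and 0.4. With 10% of readings hypertensive, a participant-clustered interval gave 5–8% at ICC 0 to 0.3.

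**The case against.** A reader might infer that the plan pools arms and that each ratio is therefore confounded. The article does not say so. It compares rates between interventions, and the paragraph before lists interventions as the three arms. The component wording can be read as the combination against each single-treatment arm, which is the clean comparison. The wording remains ambiguous: elsewhere the article names full arms when it means arm-to-arm comparisons, and here it does not.

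A reader might also infer that readings are analysed as independent. That is not stated either. The rate is recorded for each participant, a count of readings is a legitimate exposure, and variance handling is commonly left to a fuller document. This part is a request for clarification, and it does not touch AD, whose denominator is study days.

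On the decision rule, the words about no difference are a prediction, not a declared criterion for safety, and the planned interval already contains the upper limit. The any-event risks used above are also not the planned AD event rate, and hypertension counted over many readings carries more information than a yes/no outcome. These points limit the illustration. They do not supply a margin or any rule that could support a no-harm conclusion.

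The research monitor, live monitoring and adverse-event reporting protect participants during the trial. They do not repair the between-arm inference.

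**Conclusion.** The point holds in this form. The firm part is the decision rule: Hypothesis 3 asserts no harm, tests only for a significant association, and was not sized for it. For uncommon events a non-significant ratio is the expected result even under a two- to threefold increase in risk, and an observed ratio of 1 could leave roughly 0.25 to 4.0 open. Those sizes rest on assumed participant-level risks of 10–30% in the comparison arm and would improve with commoner events.

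The other two parts are conditional. The 0.75 factor applies only if arms are pooled, risks multiply and stimulation doubles risk. The 1.8- to 3.2-fold narrowing applies only to hypertension, only if readings are treated as independent, and at an assumed ICC of 0.1 to 0.4 with 24 readings. The documents do not support saying that the plan is confounded or that its intervals are wrong. They do support saying that the text leaves both possible.

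**What to change.** Before unblinding, amend the analysis text for hypertension and AD as follows.

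1. Name two safety contrasts: tAIH + WALK_tSTIM versus Placebo + WALK_tSTIM for the tAIH component, and tAIH + WALK_tSTIM versus tAIH + WALK_tSHAM for stimulation. State that arms are not pooled.
2. Estimate rate ratios with a participant-level or cluster-robust model and a log-exposure offset (readings for hypertension, study days for AD). A negative binomial model, or generalised estimating equations with robust standard errors, would serve.
3. Base the safety statement on the 95% interval and its upper limit, and say that a non-significant ratio does not establish absence of harm. Without an upper limit fixed in advance, present the result as estimation only.

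This changes wording and code only and needs no new data or participants. The cost is wider intervals and a more modest safety claim.

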### Experiment protocol

We developed a study protocol to measure the extent to which tAIH priming boosts the efficacy and potency of training-related functional gains in persons with chronic SCI (Fig. 1). Study participants enroll in 23 intervention and assessment sessions at one of the two clinical trial sites (Fig. 3). Physical therapists serve as trainers and raters; they complete competency and protocol training before their study involvement to ensure rater and training reliability within and between the clinical sites. The interventions consist of eight sessions of walking practice followed by eight combinatorial treatment sessions (four sessions per week for 4 consecutive weeks).

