#### Protection against cardiopulmonary risk

During interventions, a team member monitors cardiopulmonary function to ensure safety and comfort. If excessive discomfort or pain is reported, the intervention ends. In case of medical issues that may arise during our interventions, such as symptoms of autonomic dysreflexia (AD), rapid change in HR or systolic BP (SBP), diaphoresis, severe headache, or dizziness, participants will be withdrawn from the experiment and provided skilled care from the research clinicians. The emergency medical team at the clinical sites are notified promptly. Return to the study requires medical clearance.

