#### Autonomic dysreflexia incidence rate

AD incidence rate is the number of AD events divided by the total person-time (number of study days completed by each participant) to account for the total number of chances for detecting AD for days not measured because of dropout or a disqualifying adverse event.^47^ An AD event will constitute a participant having a SBP increase from baseline of 20 mm Hg not associated with exercise or SBP >150 mm Hg with complaints of headache, diaphoresis, and/or blurred vision and will be diagnosed by our study team clinicians (physicians and physical therapists).

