To minimize biases and errors in data collection, a designated lead physical therapist, blinded to study interventions, ensures participant adherence to the protocol and consistent scoring among therapists by regularly checking all assessment logs for adherence to standard clinical procedures. Non-blinded research staff members (including post-doctoral fellows, lab engineers, and research assistants) assist clinicians with training setup and clinical data collection. The study principal investigator oversees all study procedures and ensures the correct collection and documentation of data. If participants miss more than two walking practice sessions or intervention sessions, we will not conduct further assessments and exclude their data from analyses. However, if participants miss an assessment session, we record their data as “missing” at that time point.

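### Excluding randomised participants who miss more than two intervention sessions, and ending their assessments, removes the protection of randomisation and conflicts with how the hypertension and autonomic dysreflexia rates are defined

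*Protocol article*

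**What the plan says.** The last paragraph of Statistical analysis in the protocol article gives the rule: "If participants miss more than two walking practice sessions or intervention sessions, we will not conduct further assessments and exclude their data from analyses". No analysis is exempted. The next sentence treats a missed visit differently: "However, if participants miss an assessment session, we record their data as “missing” at that time point".

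Other sections fix what the rule means:

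- **Timing of assignment.** Under Randomization, participants are assigned "in the order in which they complete the walking practice sessions".
- **Number of sessions.** Experiment protocol describes "eight sessions of walking practice followed by eight combinatorial treatment sessions", so the rule applies from the third missed intervention session.
- **Route from harm to missed sessions.** Under Protection against cardiopulmonary risk, after AD symptoms, rapid heart rate or systolic pressure change, severe headache or dizziness, "participants will be withdrawn from the experiment and provided skilled care from the research clinicians". Return is possible with medical clearance. Protection against low oxygen risks stops the experiment for similar symptoms.
- **Safety rates.** Autonomic dysreflexia incidence rate uses person-time "to account for the total number of chances for detecting AD for days not measured because of dropout or a disqualifying adverse event". The Blood pressure section makes the same allowance for the hypertension rate.
- **Attrition.** Sample size plans 20 per group: "Assuming a 20% dropout rate with 16 completers per group".

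**The concern.** Missing walking practice comes before assignment, so excluding people for it does not disturb the randomised comparison. Missing intervention sessions comes after assignment. The arms can differ in how many people reach three missed sessions and why: symptoms during low-oxygen breathing, discomfort from stimulation, or no perceived benefit. Once those people are removed, the remaining groups need not be comparable.

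Three things are at stake:

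- **Efficacy (Hypothesis 1).** The between-arm differences describe only those who attended enough sessions.
- **Safety scores (Hypothesis 3).** Spasticity (SCATS), pain (NPRS), cognition (CVLT3, O-TMT), bowel (NBDS) and bladder (NBSS) scores have no allowance for dropout. A conclusion of no maladaptive change would rest on a group from which some affected participants may have been removed.
- **Consistency.** The hypertension and AD rates make sense for people who drop out or are disqualified only if their partial data are kept, whereas the exclusion rule, read plainly, discards them.

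The rule also stops data collection. An analysis plan written later could redefine the analysis set, but it could not recover week-4 and follow-up measurements that were never taken.

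**Working it through.** **1. The plan's own figures.** Inputs from Sample size: SD of 10-Meter Walk Test change 3.0 s (combination) and 2.0 s (comparators), 16 completers per arm, alpha 0.0167 (two-sided assumed), differences -3.14 s and -5.2 s. Welch t-test:

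- SE = sqrt(3²/16 + 2²/16) = 0.901 s, df = 26.1.
- 3.14/0.901 = 3.48, power 81.5% (stated: above 81%).
- 5.2/0.901 = 5.77, power 99.9% (stated: above 99%).
- 16/(1 - 0.20) = 20 per arm, 60 in total.

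The stated figures reproduce, so the design is powered on those who complete.

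**2. What exclusion can do when there is no true effect.** Assumptions: 20 per arm, the SDs above, and positive change meaning slower. The article does not say how many people the rule would remove, so the numbers excluded are illustrative. In 20 standard normal values the eight worst average about 0.927 SD. Removing k participants at random from those eight shifts the mean of the rest by k × 0.927 × SD/(20 - k), towards better performance:

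- Combination arm, k = 4: 4 × 0.927 × 3/16 = 0.70 s.
- Combination arm, k = 2: 2 × 0.927 × 3/18 = 0.31 s.
- Comparator arm, k = 4: 4 × 0.927 × 2/16 = 0.46 s.

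Simulation with a Welch test at 0.0167 gives:

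| Who is excluded | Bias (combination minus comparator) | Type I error |
|---|---|---|
| 4 of worst 8 in combination, 4 at random in comparator | about -0.7 s | about 5% |
| 2 of worst 8 in combination, 2 at random in comparator | about -0.3 s | 2.1% |
| 4 of worst 8 in both arms | about -0.2 s | 1.8-1.9% |
| 4 at random in combination, 4 of worst 8 in comparator | about +0.5 s | not tabulated |
| 4 at random in each arm | none | about 1.7% |

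**3. Power if all 20 per arm are analysed.** Suppose 4 of 20 in the combination arm are non-adherent and keep a fraction f of the benefit. The mean difference is 3.14 × (0.8 + 0.2f). Mixing two kinds of participant raises the combination-arm variance to 9 + 0.16 × [3.14(1 - f)]².

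- f = 1: difference 3.14 s, SD 3.00, power 90.8%.
- f = 0.5: difference 2.83 s, SD 3.07, power 81.8% (83% with SD held at 3.0).
- f = 0: difference 2.51 s, SD 3.25, power 66.1% (72% with SD held at 3.0).

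For the -5.2 s contrast, power stays at 96.8% or more throughout.

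**The case against.** Several stronger readings are tempting and go beyond the documents.

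- **That AD and hypertension events are deleted from the safety rates.** The exclusion sentence can be read so. But the rate definitions are specific and may be meant to override a general sentence, and Adverse event reporting records events from enrolment to the last follow-up. The documents support an unresolved conflict, not a settled deletion. Illustrating it with a proportion of participants would also be wrong, because the AD rate is events per person-time.
- **That those removed are the ones most harmed.** This is an inference from the withdrawal provisions. Return after clearance is possible, and one event need not lead to three missed sessions.
- **That the analysis is of completers only.** Participants who miss one or two sessions stay in, as do those who miss an assessment visit.
- **That the whole 20% attrition comes from this rule, or that the bias favours the combination.** Neither is stated. Losses during follow-up do not trigger the rule, and the table above shows bias in either direction or none.

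It is also fair that simply retaining everyone does not settle every analysis. The mixed model for Hypothesis 1 accommodates incomplete follow-up, but the Friedman test for Hypothesis 3 needs complete blocks. The Hypothesis 2 outcome, sessions to reach the minimal clinically important difference (MCID), is unclear for someone who stops early.

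These points limit the claim about size and harm. They do not remove the core problem: a stated rule excludes randomised people on a post-randomisation event and ends their measurement.

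**Conclusion.** The point holds in this form. For intervention sessions, the rule makes inclusion in the efficacy and Hypothesis 3 comparisons depend on attendance after randomisation, which treatment may affect. It also contradicts the allowance for dropout in the hypertension and AD rates, and these sections must be reconciled. The walking-practice half of the rule is not at fault.

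The size cannot be determined from the article. The 10-Meter Walk Test scenarios assume two or four exclusions per arm, normally distributed changes with the planning SDs, no true effect and a chosen pattern of selection. Within them, bias ranges from about -0.7 s to about +0.5 s, and is nil if exclusion is unrelated to outcome. For scale, the smaller planned difference is 3.14 s. Because excluded participants would not be measured further, the trial could not show which scenario applied.

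**What to change.** - Apply the walking-practice part of the rule only before randomisation.
- For randomised participants, separate stopping the intervention from stopping assessment. Continue scheduled assessments where the participant consents and is medically cleared, with no change to any safety withdrawal rule.
- Analyse all randomised participants as assigned in the primary efficacy analysis, using the planned mixed model.
- Include everyone who received any combined session in the safety analyses, with all data collected, so that the exclusion sentence agrees with the hypertension and AD rate definitions.
- Keep exclusion for more than two missed intervention sessions as a per-protocol sensitivity analysis.
- For Hypothesis 2, treat participants who stop before reaching the MCID as censored, using the survival-type analysis already named under Study limitations.
- For Hypothesis 3, replace the Friedman test with a rank or mixed method that allows incomplete data.

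The cost is revised wording, some extra follow-up visits and possible dilution. N stays at 60. The sponsor should state that, if four of 20 in the combination arm lose all benefit, the -3.14 s contrast becomes 16 × (-3.14)/20 = -2.51 s with power of about 66-72%, against the stated figure of above 81%. Power is about 82-83% if they keep half the benefit and about 91% if they keep all of it.
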